**Baseline surveys**										
	Self-Care of HF Index		Research nurse	✓	—	—	—	—	—	—
	Minnesota Living with HF Questionnaire		Research nurse	✓	—	—	—	—	—	—
	Dutch HF Knowledge Scale		Research nurse	✓	—	—	—	—	—	—
Primary outcome: Self-Care of HF Index			Research assistant	—	—	—	—	✓	✓	✓
**Secondary outcomes**										
	HF knowledge		Research assistant	—	—	—	—	—	—	✓
	HF quality of life		Research assistant	—	—	—	—	✓	✓	✓
	All-cause hospitalization (yes/no)		Research assistant	—	—	—	—	✓	✓	✓

^a^-*t*_1_: Time at enrollment.

^b^*t*_x_: Time at the end of study.

^c^*t*_1_: Time at allocation.

^d^*f*_1_: Time at first month follow-up; *f*_2_: Time at second month follow-up; *f*_3_: Time at third month follow-up.

^e^HF: heart failure.

^f^Not applicable.

^g^NYHA: New York Heart Association.

**Figure 5 figure5:**
[figure not shown]
Schematic representation of the study design. HF: heart failure.

### Sample Size

In this study, the sample size was calculated based on the minimal clinically important difference (MCID) approach for self-care as measured by SCHFI for the primary outcome. No specific MCID for SCHFI was available to the best of our knowledge and based on our search of the PubMed database.

The suggested MCID for assessing dyspnea with the visual analog scale (0-100 score index) was the range 10-20 [56]. Thus, improving self-care for ≥10 scores from the baseline at the end of the study has been considered as MCID for the present study in order to reach a large sample size. According to the Jurgens et al [22] study in 2013, a mean of 70.8 for self-care in the control group at the end of study (90-days) and a fixed standard deviation of 27.2 (the largest SD) have been considered. In order to calculate sample size by G*Power free software (version 3.1.9.2), the input parameters are as following: effect size (Cohen *f*) of 0.168, the alpha error probability of .05, a statistical power of 80% to detect MCID≥10 scores between the 2 groups at the end of the study, 3 times measurement of outcome with monthly intervals, and a correlation coefficient of .5 among repeated measurements. Thus, by considering the overall attrition rates of 10%, the sample size was set at 68 participants (34 participants in each group).

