### Study Measures

#### Primary Outcome

##### Self-Care Behavior

Effective self-care improvement is a priority of all clinicians caring for patients with HF [46]. In a developing country like Iran, there is a growing need to improve patient’s self-care [15]. However, there is a low rate of reported admissions for HF in Iran [3]. Thus, in contrast to previous studies where hospitalization was considered the primary outcome [21,22,30] and self-care as the secondary outcome [21,22], self-care has been identified as the primary outcome in this trial.

Self-care behavior will be measured by the Self-Care of Heart Failure Index (SCHFI) version 6.2 [47] by self-reporting at baseline and monthly intervals for 3 months. SCHFI was translated into Persian and validated for Persian speaking people by Siabani et al in 2014 [48]. It consists of 3 separate scales and 22 questions: 10 for self-care maintenance, 6 for self-care management, and 6 for self-care confidence [49]. Cronbach alpha was determined for self-care maintenance (.56), management (.64), and confidence scales (.79) [48]. Scale scores can range between 0 to 100, and a score ≥70 will be considered as adequate self-care [49]. We will ask participants to complete SCHFI by themselves at baseline and then monthly for 3 months.

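### The 10-point self-care target is stated both as a gain from baseline and as a between-group difference, and the entered Cohen f of 0.168 does not match 10 points between groups at SD 27.2 (f = 0.184)

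*Protocol article*

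**What the plan says.** All design inputs are in the Sample Size section. It states that "No specific MCID for SCHFI was available to the best of our knowledge" and takes the value from another instrument: "The suggested MCID for assessing dyspnea with the visual analog scale (0-100 score index) was the range 10-20". It then sets the target as "improving self-care for ≥10 scores from the baseline at the end of the study has been considered as MCID for the present study". Later in the same paragraph, the G*Power inputs include "a statistical power of 80% to detect MCID≥10 scores between the 2 groups at the end of the study", an "effect size (Cohen *f*) of 0.168" and "a fixed standard deviation of 27.2 (the largest SD) have been considered". The other inputs are alpha .05, three monthly measurements and a correlation of .5 among them. With 10% attrition the total is 68, or 34 per group.

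Two other places bear on what the target should be. The Self-Care Behavior section says that the SCHFI has three separate scales, each scored 0 to 100; the Sample Size section does not say which one the 10 points refer to. The Primary Analysis section plans to average the monthly self-care scores and compare that mean between the groups, and the abstract's primary objective is likewise a comparison between groups.

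**The concern.** A gain of 10 points from baseline and a difference of 10 points between arms are different quantities. If the control arm also improves, a 10-point gain under the intervention corresponds to a smaller group difference. The objective and the planned comparison are both between groups, so the reference to baseline is the wording that does not fit.

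The effect size is the number on which the calculation rests. If it cannot be obtained from the stated difference and SD, a reader cannot tell which difference the trial is powered for. The stakes are larger than a rounding gap, because the meaning of f depends on which repeated-measures test it is entered into. The stated 80% power can be credited to a 10-point group difference only if f and the test both refer to group differences.

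**Working it through.** **Inputs.** From Sample Size: difference 10 points, SD 27.2, f = 0.168, alpha .05, power 80%, m = 3 measurements, correlation ρ = .5, attrition 10%, two equal groups. Assumed here: F tests under sphericity, no baseline adjustment unless stated, and 68 × 0.9 = 61.2 completers, taken as 62 (31 per arm).

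**1. Reproducing the plan's 68.**
- Within-subject or group-by-time test: λ = f²·N·m/(1 − ρ). With f = 0.168 and N = 60, λ = 0.0282 × 60 × 3/0.5 = 10.2 and power is 0.811, so N = 60 is enough. Then 60/0.9 = 66.7, which is 67, or 68 with equal arms. This matches the plan.
- Between-groups test: λ = f²·N·m/(1 + (m − 1)ρ). With f = 0.168 it needs N = 188, or 209 after attrition. This does not match.
- Counting baseline as a fourth measurement (m = 4), the within or interaction test gives 50, or 56 after attrition, and the between-groups test 176, or 196. Neither matches.

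**2. Converting the stated target to f.** For two equal groups, f = difference/(2 × SD).
- 10/(2 × 27.2) = 0.184, not 0.168.
- Read backwards, 0.168 is 2 × 0.168 × 27.2 = 9.1 points, or 10 points at an SD of 10/(2 × 0.168) = 29.8.

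**3. What f means in the formula that reproduces 68.** For the interaction test, f measures how far the group difference changes across visits.
- A constant 10-point difference (10, 10, 10) has interaction f = 0.
- A difference growing linearly (0, 5, 10) has f = 0.075, with power about 0.23 at N = 62. Reaching 0.168 on that pattern needs 10 × 0.168/0.075 = about 22 points at the last visit.

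**4. The stated target in a test that matches it.** Between-groups test, f = 0.184, m = 3, ρ = .5:

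| Quantity | Result |
|---|---|
| N for 80% power | 158 analysed, 176 enrolled |
| Power with 62 completers | about 41% |
| Power with all 68 | about 45% |

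The SD of a three-visit mean is 27.2 × √((1 + 2 × .5)/3) = 22.2. With 31 per arm, the difference detectable at 80% power is (1.96 + 0.84) × 22.2 × √(2/31) = about 15.8 points. For a single comparison at the last visit it is about 19.4 points, and power for 10 points is about 30%.

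**5. Correcting f alone.** Putting 0.184 into the within or interaction formula gives N = 50, or 56 after attrition. That would shrink the trial and leave the mismatch of test and target in place.

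**The case against.** Several points on the other side stand.

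- **The origin of 0.168 is unknown.** The conversion to 9.1 points applies to a between-groups f, and the plan's N does not come from a between-groups test. Read as a time effect, a 10-point gain over three visits with means (0, a, 10) gives any f from 0.150 to 0.173; a = 0.65 or 9.35 gives 0.168. So 9.1 points is one reading. Still, a time effect is not the between-group target that the section claims to power, so the mismatch remains.
- **The smaller f is conservative.** Within any one formula, 0.168 asks for more patients than 0.184. The entry by itself does not weaken the trial.
- **The borrowed value is disclosed.** A reader might infer that the trial has no valid threshold at all. The text does not support that: it says that no SCHFI value was found, names the dyspnea scale and takes the low end of its range. The justification is weak but open, and calls for the label of planning assumption.
- **No within-arm claim is planned.** A reader might infer that gains from baseline will be reported as clinically important although chance or measurement error could produce them. Nothing in the article proposes a responder analysis or a within-arm conclusion. In randomized arms, the difference in mean change and the difference in end means have the same expectation. Nor can measurement error be derived from the article: the reliability coefficients and the SD come from different studies, and a single SD would have to serve three scales. The mean of 70.8 is an end-of-study control value from a cited study, so it cannot show how many patients start near the ceiling.
- **Baseline adjustment would help.** With baseline as a covariate at the same correlation, power on the three-visit mean with 31 per arm is about 61%. The Primary Analysis section does not state such an adjustment, and the figure is still short of 80%.

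**Conclusion.** The point holds as an inconsistency in the Sample Size section that should be corrected. The 10-point target is given two meanings, and f = 0.168 is not the effect size for 10 points between two equal groups at SD 27.2, which is 0.184. The planned 68 is reproducible, but only under a within-subject or interaction formula, so the stated 80% power does not belong to a 10-point difference between groups. For that difference, averaged over three visits, power is about 41% with 62 completers and 45% with 68, and the detectable difference is about 16 points.

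These figures rest on the article's SD and correlation, on sphericity, equal arms and no baseline adjustment. The conclusion about the two definitions and the value of f needs only the SD and the between-groups conversion. It does not extend to saying that the 10 points are invalid as a target or that the trial intends to claim benefit from gains within an arm.

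**What to change.** In the Sample Size section:

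1. Remove the reference to baseline and define the target once, as a between-group mean difference of 10 points on a named SCHFI scale. Name the time point, or use the mean of the monthly scores so that it agrees with the Primary Analysis section.
2. Call the 10 points a planning assumption borrowed from a dyspnea scale, since no SCHFI value was available.
3. Derive f = 10/(2 × 27.2) = 0.184 from it and use it in a between-groups test. Do not change f alone, and do not reduce N.
4. Restate what 68 participants give: power of about 41% with 62 completers and 45% with 68, or a detectable difference of about 16 points on the three-visit mean. If a baseline-adjusted analysis is intended, say so and give its power instead.

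The cost is a few sentences and one rerun of the calculation. The real price is that the 80% figure for a 10-point group difference has to be withdrawn, unless the number of analysed participants rises to about 158.

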### Statistical Methods

Statisticians will prepare the data sheets to collected data. Data will be entered into the SPSS software (version 16). The Kolmogorov-Smirnov test will be used to normality. A transformation approach will be used to handle non-normal distribution. For the between-group comparison of continuous and categorical baseline characteristics, independent *t* test and chi-square test will be used. For categorical variables between the 2 groups, the two-tailed Fisher exact test will be used instead of the chi-square test in the case of too small expected cell frequencies. A *P* value <.05 will be considered statistically significant.

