#### Primary Analysis

Baseline scores for each scale of SCHFI including self-care maintenance, management, and confidence will be compared in both groups by an independent *t* test. Due to the measurement of self-care behavior at baseline and at monthly time intervals, we will calculate the mean of monthly self-care scores in order to compare the mean of self-care behavior after the intervention in both groups. Also, because of the frequent measurement of self-care behavior, we will also use *P* value correction based on the Bonferroni method [58]. A linear logistic regression procedure will be applied to determine the factors affecting self-care behavior. The odds ratio will be reported with 95% CI.

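### The stated 80% power for a 10-point between-group difference does not follow from the sample-size inputs; with 68 patients it is about 30% at the end of the study and about 42% for the mean of the monthly scores

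*Protocol article*

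**What the plan says.** The Sample Size section first defines the minimal clinically important difference (MCID) as a change within patients: "improving self-care for ≥10 scores from the baseline at the end of the study has been considered as MCID". It then uses the same 10 points as a contrast between groups, claiming "a statistical power of 80% to detect MCID≥10 scores between the 2 groups at the end of the study". From a cited earlier trial it takes a control-group mean of 70.8 at 90 days; for the spread of scores it says that "a fixed standard deviation of 27.2 (the largest SD) have been considered". The inputs given for G\*Power are "effect size (Cohen *f*) of 0.168", "the alpha error probability of .05", three monthly measurements and a correlation of .5 among them. Allowing 10% attrition, the total is 68, or 34 per group. The G\*Power test is not named.

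The Primary Analysis section describes a different comparison: "we will calculate the mean of monthly self-care scores in order to compare the mean of self-care behavior after the intervention in both groups". It adds a Bonferroni correction without giving the number of tests, and it describes no test of time or of group by time. The Statistical Methods section states that "A *P* value <.05 will be considered statistically significant".

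**The concern.** A 10-point difference against an SD of 27.2 is a standardised difference of about 0.37. Around 30 patients per arm is far too few to detect that between groups with 80% power, even when three follow-up scores are averaged. This is the only sample-size justification for the primary outcome. If the claim is taken at face value, a non-significant result would be read as evidence against a 10-point effect, when on the stated inputs the trial would miss such an effect more often than it found it.

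**Working it through.** **Inputs.** From Sample Size: difference 10, SD 27.2, f = 0.168, alpha .05, m = 3 measurements, correlation ρ = .5, attrition 10%, 34 per arm. After attrition, 68 × 0.9 = 61.2, so about 31 per arm. Assumed: two-sided testing (sidedness is not stated), and ρ = .5 between every pair of follow-up visits.

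**1. Reproducing 68.** Repeated-measures formulas with two groups and the noncentral F distribution:

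- Within factors, or within-between interaction: λ = N f² m / (1 − ρ), with 2 and 2(N − 2) degrees of freedom. N = 60 gives λ = 60 × 0.168² × 3 / 0.5 = 10.16 and power .811. Then 60 / 0.9 = 66.7, so 67, or 68 for equal arms. This matches the plan.
- Between factors: λ = N f² m / (1 + (m − 1)ρ), with 1 and N − 2 degrees of freedom. The N for 80% power is 188 (209 with attrition). At N = 60, power is .348. This does not match.
- Other variants, totals with attrition: within/interaction with m = 4, or with f = 0.184, gives 56. Between factors gives 196 with m = 4 and 176 with f = 0.184. A plain two-sample comparison needs 117 to 118 per arm. None gives 68.

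**2. Effect size.** For two equal groups f = difference / (2 × SD) = 10 / (2 × 27.2) = 0.184. The stated 0.168 corresponds to 0.168 × 2 × 27.2 = 9.1 points.

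**3. Power for 10 points between groups** (noncentral t):

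- End of study: d = 10 / 27.2 = 0.368.
- Mean of three monthly scores: SD = 27.2 × √((1 + 2 × 0.5) / 3) = 22.2, so d = 0.450.

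| | End of study | Mean of three |
|---|---|---|
| Power, 31 per arm | 30% | 42% |
| Power, 34 per arm (no attrition) | 32% | 45% |
| Difference detectable with 80% power, 31 per arm | 19.7 points | 16.1 points |
| Power, 31 per arm, Bonferroni over three tests (number assumed) | 16% | 25% |
| Evaluable N for 80% power | 236 | 158 |
| The same, with 10% attrition | 263 | 176 |

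The 158 uses f = 0.184. At the stated f = 0.168 the visit average needs 188.

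**4. Would a group-by-time test restore 80%?** A constant 10-point difference has no interaction (f = 0). A difference growing 0/5/10 gives cell interaction effects of ±2.5, 0 and ±2.5, so f = √((2.5² + 0 + 2.5²) / 3) / 27.2 = 0.075. At N = 62 power is then 23%. The other profiles tried that reach 10 points at month 3 (3.3/6.7/10, 0/0/10, 0/10/10) give f between 0.05 and 0.087 and power of about 12% to 30%.

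**The case against.** The strongest defence is that the trial is longitudinal, that a repeated-measures calculation is a reasonable basis, and that a condensed article need not name every software option. It is also fair to say that the SD was deliberately cautious, being described as the largest available, and that f = 0.168 is smaller than 10 points would imply.

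Part of this stands. The cautious SD matters: at 31 per arm the mean of three would reach 80% power if the SD were about 16.9. But the article offers no smaller SD, and it does not say which of the three SCHFI scales 27.2 belongs to. The discrepancy in f is conservative: 0.184 would have lowered the within/interaction N to 50. The change-from-baseline wording of the MCID largely coincides with a between-group difference if the groups start equal and controls do not change. Both are secondary.

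The defence does not rescue the 80%. No group-by-time test is planned, and such a test would have low power for a 10-point difference. Even with zero correlation between visits, contrary to the stated .5, the three-month mean would reach only about 69%.

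A reader might go further than the document allows in four ways:

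- **That 68 is known to come from the interaction option.** It is only inferred. Within factors and within-between interaction give the same N and cannot be told apart.
- **That 188 is what the stated target requires.** That figure concerns the average over three visits. A single end-of-study contrast needs about 236.
- **That 42% is the power of the planned analysis.** It ignores the Bonferroni correction in Primary Analysis and is an upper figure until the number of tests is fixed.
- **That baseline adjustment supplies a better power figure.** No ANCOVA is planned, and its power would rest on a baseline correlation that the article does not give.

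**Conclusion.** The claim is wrong as written. On the article's own inputs, 68 patients do not give 80% power for a 10-point difference between groups. Power is about 30% for the contrast named in Sample Size and at most about 42% for the one named in Primary Analysis. With no attrition these become 32% and 45%. The size of the shortfall rests on SD 27.2, ρ = .5 and two-sided alpha .05; any Bonferroni correction widens it. How 68 was obtained is an inference, but the conclusion does not depend on it.

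**What to change.** Keep the sample size at 68 and correct the Sample Size section:

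1. Withdraw the claim of 80% power for 10 points.
2. Have the sponsor name the G\*Power test actually used.
3. Give f = 0.184 for 10 points at SD 27.2.
4. State one target contrast, worded as a between-group difference, that matches the primary analysis.
5. Restate power and the detectable difference for that contrast at the alpha to be used after any Bonferroni correction, giving the number of tests. Without correction, the mean of the monthly scores has about 42% power and a detectable difference of about 16 points.
6. State that the 95% CI for the difference will be read against the 10-point MCID, so that a non-significant result is not taken to exclude it.

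ANCOVA power should be printed only if the analysis is changed to ANCOVA, and then over a range of baseline correlations. The cost is wording and a less favourable power figure; no extra patients are needed.

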### Participant Recruitment

During the run-in phase of the study, the research nurse at the HF clinic will be present Sunday through Wednesday of each week from 8 am to 1 pm. The nurse will screen the patients for the eligibility criteria at the time of admission. Participant screening will continue until the target population is achieved. Simultaneously, an HF specialist will confirm the subject`s eligibility and adjust the drug dosages of the eligible participants. Also, the specialist will provide each patient with additional details about the study. This is our main strategy for achieving adequate participant enrollment.

### Allocation: Method and Concealment Mechanism

The block balanced randomization method will be used for allocation. Before initiation of the run- in phase of the study, the statistician ([name]) will generate the randomization plan by website Randomization.com [57]. Therefore, twenty blocks of 4 for both the intervention group (group A) and the control group (group B) will be prepared. The statistician will fold the paper containing 4-size blocks 2 times, put them in the standard envelopes and write the serial numbers on them. All envelopes will be kept at the recruitment center. Thus, for every eligible patient, the research nurse randomly selects one of the envelopes after shuffling and assign participants into intervention and control groups.

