### Intervention

In this study, the intervention is an integrated package consisting of 3 components: (1) HF self-care education, (2) regular home self-monitoring of weight and SOB, and (3) scheduled call follow-ups.

The first component of the package includes HF self-care education that will be delivered in the HF clinic of the THC according to the Australian Heart Foundation educational booklet entitled “living well with chronic HF” [38]. Individual education will be provided by the research nurse (MN) according to the participants understanding and literacy for a 40-minute face-to-face session between 8 am to 1 pm. A Farsi version of the booklet will be given to each participant. Also, during the educational session, the instructor and the participant will review the booklet content together, and the instructor will answer any questions. The booklet contains information on disease definition, diagnosis, symptoms, and ways to manage them, lifestyle issues, medicines, and other treatments. In order to obtain permission to translate the booklet to Farsi language for local use in Iran, one of the authors (MN) contacted the Australian Heart Foundation on April 5, 2016. After obtaining permission, it was translated to the Farsi language by an individual who was also proficient in the English language and knowledge of cardiovascular terminologies. Two nursing faculty members and 2 cardiology faculty members affiliated with TUMS approved the Farsi version of the booklet.

Participant eligibility criteria.

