### Ethics Approval and Consent to Participate

The study protocol, data collection forms, educational booklet, and the template of informed consent form was reviewed and approved by the Research Ethics Committee (REC) at TUMS on February 5, 2017 (No. IR.TUMS.FNM.REC.1395.1653). Researchers are committed to updating the agreement with the IRB and REC at TUMS for any administrative and methodological changes of the study protocol which may affect the study.

In order to obtain the informed consent, the research nurse and HF specialist will introduce the trial to each eligible participant. Every eligible participant will receive an information sheet and a written informed consent. The research nurse will then obtain written informed consent from all participants willing to participate in the trial.

The participant informed consent form will be prepared according to the Declaration of Helsinki. It gives the subject information on what the research is about and what happens following participation in the study. It contains information on “purpose of the trial, potential benefits and risks; subject`s right to refuse participation or to withdraw consent at any time; institutional affiliation and potential competing interests of the researcher; and sources of trial funding” [59].

One critical issue that the researchers will be experiencing is posttrial care. Due to the nature of the intervention, this trial will not have any harm for participants that need to be treated during or after the trial. However, the HF specialist is the responsible physician and will assess and manage participants in the event of worsening of the symptoms.

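### The envelope procedure contradicts itself, and under no reading does it give both concealed allocation and balanced blocks

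*Protocol article*

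**What the plan says.** Under Allocation: Method and Concealment Mechanism, the statistician generates the list before the run-in phase, and "twenty blocks of 4 for both the intervention group (group A) and the control group (group B) will be prepared". The statistician is then to "fold the paper containing 4-size blocks 2 times, put them in the standard envelopes and write the serial numbers on them". On storage: "All envelopes will be kept at the recruitment center". On use: "for every eligible patient, the research nurse randomly selects one of the envelopes after shuffling and assign participants into intervention and control groups".

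One role runs through the whole entry process. Participant Recruitment says "The nurse will screen the patients for the eligibility criteria at the time of admission". Ethics Approval and Consent to Participate says "The research nurse will then obtain written informed consent from all participants willing to participate in the trial". Table 1 names the research nurse as the staff member for allocation. The Intervention section says "Individual education will be provided by the research nurse", and it gives the same nurse the diary training and the scheduled calls.

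Three safeguards are stated. An HF specialist confirms eligibility (Eligibility Criteria; Participant Recruitment). Participants complete the baseline surveys themselves before randomization (Data Collection). The outcome assessor is blinded (Blinding).

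**The concern.** A block of 4 in each envelope does not fit one envelope per patient. Serial numbers do not fit shuffling, because they no longer fix the order of use. A reader cannot tell what a single envelope contains or how many patients it serves, and those two facts decide whether allocation is concealed and whether the arms stay balanced.

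The exposure is real in this trial. The nurse delivers the intervention and so knows every past assignment, holds the envelopes on site, and influences whom to approach and when. Participants know their group and report the primary outcome (SCHFI) themselves. If the nurse knows the next assignment, an eligible patient can be deferred or passed over, and the groups then differ at entry. A blinded outcome assessor does not prevent that, and analysis cannot reliably repair it.

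**Working it through.** **Inputs.** 20 blocks of 4 (Allocation section). 68 patients, 34 per arm (Sample Size). One research nurse who screens, takes consent, allocates and treats (sections cited above).

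**Supply.** 20 × 4 = 80 assignments, 40 per arm. 68 patients need 68 / 4 = 17 blocks. The stock is large enough only if each block envelope serves four patients, or if there are 80 envelopes with one assignment each.

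**Reading (a): one block per envelope, used for four patients.**
- Any 17 complete blocks end at 34:34, and the arm difference never exceeds 2 on the way. Shuffling whole blocks does no harm to balance.
- The first opening of each envelope exposes the next three assignments: 17 × 3 = 51 of 68 (75%) are known before the patient is enrolled.
- It conflicts with a draw for every eligible patient.

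**Reading (b): one block envelope drawn per patient, as literally written.**
- 20 envelopes serve 20 patients, and 68 − 20 = 48 patients have none.
- Nothing says which of the four entries on the sheet applies.

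**Reading (c): 80 single-assignment envelopes, shuffled.**
- The nurse cannot read the next assignment from a sheet, but the order in the blocks is gone. The number in one arm after n patients is hypergeometric: n draws without replacement from 80, of which 40 are for that arm.
- P(34:34 at n = 68) = C(40,34) × C(40,34) / C(80,68) = 3,838,380² / 60,246,643,120,300 = 0.245.
- The other probabilities come from summing the same distribution:

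| Event | Shuffled slips | Intact blocks of 4 |
|---|---|---|
| Exactly 34:34 at 68 | 0.24 | 1 |
| Arm difference >2 after 34 patients | 0.50 | 0 |
| Arm difference >2 at 68 | 0.35 | 0 |
| Arm difference ≥8 at 68 | 0.025 | 0 |

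**Side by side.** (a) keeps the blocks and loses concealment. (b) runs out of envelopes. (c) can hide the next assignment but is not the block-balanced method that the section announces, and the enrolling nurse still picks the envelope.

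**What serial order alone would leave open.** Suppose the envelopes held one assignment each and were opened in order, with blocks fixed at 4 and a nurse who knows that size and sees past assignments. Enumerating the 6 possible blocks (24 positions), 8 of 24 assignments (1/3) are certain from what went before. Guessing the arm with more places left is right in 17 of 24 (71%). So the block size has to be withheld.

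**The case against.** The strongest reply is that the wording is loose and does not say one block per envelope. A draw for every eligible patient also fits 80 single slips, and then nobody sees the sequence in advance. That stands. A reader might infer that the procedure certainly reveals assignments; the text supports this only under reading (a), and the figure of 51 of 68 is conditional on it.

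A reader might also infer that shuffling turns the design into simple randomization. For independent fair draws (Binomial with 68 patients and probability 0.5), P(34:34) is 0.096 and P(difference ≥8) is 0.396. That would require envelopes to be returned and redrawn, which the article does not say. With a finite stock of 40 per arm, the matching figures are 0.24 and 0.025.

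Three more points deserve weight. The specialist's check, the self-completed baseline surveys before randomization and the blinded assessor all lower the risk. None of them stops a nurse who knows the next assignment from not approaching or deferring a patient. A log of drawn serial numbers would leave an audit trail despite the shuffling; the article neither describes nor excludes one, so a claim that the order cannot be audited goes too far. Finally, a condensed article may leave out that envelopes are sealed and opaque. The point does not rest on that omission: it concerns the steps that are stated and do not fit together.

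**Conclusion.** The allocation procedure is internally inconsistent, and no reading of it for 68 patients delivers both concealment and block balance. The size depends on the reading: 51 of 68 assignments foreseeable under (a), 48 patients without an envelope under (b), and a 0.35 chance of a final arm difference above 2 under (c). Large imbalance under (c) is unlikely (about 0.025 for 8 or more), so there the loss is mainly that of the announced method and the nurse's free choice of envelope. These figures assume 68 patients, 80 assignments split 40:40 and, for (c), draws without replacement. The documents do not show that selection took place. They show that the plan as written does not guard against it, in a trial where the enrolling nurse also treats and the primary outcome is self-reported.

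**What to change.** For any patients still to be enrolled, state and use one workable procedure:

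- A permuted-block list with varying block sizes that are not disclosed to recruiters.
- Sequentially numbered, opaque, sealed envelopes with one assignment each.
- Opening strictly in serial order, without shuffling, after consent and baseline surveys (the order already planned).
- Holding and opening, or reading out by phone, by the statistician or another existing team member who does not recruit, with serial number and time logged.

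The cost is a new list, a set of envelopes and a short step per patient for existing staff. The sample size does not change.

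Recruitment may already be closed: the Results section expects study completion in November 2017, while the abstract calls the study ongoing with completion by the end of 2018. If it is closed, the trial report should set out exactly how the envelopes were used and the order of allocation, and state possible selection bias as a limitation instead of claiming concealed block randomization. The same account is needed for patients already allocated if recruitment continues. This costs only reporting.
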